## Background

Keloid scars affect 10–15% of all wounds and represent an exaggerated healing response that poses a challenge for physicians. They can appear anywhere on the body and can last for years after the initial injury [1]. Patients at risk of keloid scars are usually younger than 30 years and have darker skin. Darkly pigmented skin is the primary risk factor for keloids, which has a 15–20 fold increased risk due to melanocyte-stimulating hormone anomalies. Black, Hispanic and Asian persons are more likely to develop keloid scars than Caucasians. Keloid scars are more than just disfiguring cosmetically; many are also pruritic and painful. They also often result in severe emotional distress [2].

Keloid scars are associated with deteriorated mental health during the post-natal period and can contribute to negative body image, impaired intimate relationships and symptoms of depression. Patients with keloid scars have been reported to be unhappy with their scars due to their perceived stigma and psychological association [3–6]. Consequently, this can result in these patients being unsociable and may interfere with their communication skills, personal relationships and work, life and leisure activities. Patients are usually concerned about the diagnosis and persistent nature of the scars and report that non-empathic management by general physicians and frustrations of current treatment compound their distress [6].

Any kind of trauma that can reach the reticular dermis and cause cutaneous injury (such as insect bites, burns, surgery, vaccinations, skin piercings, acne, folliculitis, etc.) can create abnormal wound healing and trigger keloid scar formation in predisposed people. The abnormal wound healing is described by continuous and histologically localised inflammation and increased inflammatory cells, which result in the increase of fibroblasts, proinflammatory factors, newly made blood vessels and collagen deposits. These changes can stimulate chronic inflammation, which in turn causes the invasive growth of keloid scars. In addition, the upregulation of proinflammatory factors in pathological scars suggests that keloid scars are inflammatory conditions of the reticular dermis of the skin [7, 8].

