Based on the cellular mechanism of keloid formation, one of the first-line options to treat keloid scars is corticosteroid injection into the affected area. The steroids have both direct anti-inflammatory and vasoconstrictive effects. Administration of corticosteroids results in the whitening of keloid scars, suggesting a decrease of blood flow in the scar due to vasoconstriction [7].

Another suggested treatment of keloid scars is surgical removal of the scar. However, since surgical removal of the keloid usually only provides temporary cosmetic relief and invariability followed by even more aggressive regrowth of scar tissue in 50–100% of cases, many clinicians perform surgical excision of the keloid scar followed by sub-dermal corticosteroid injections. This has been suggested to be effective for patients with small or single site lesions [9].

Some studies have used immediate wound edge corticosteroid injection after the excision in patients with hypertrophic scars and keloid scars, followed by regular injection of corticosteroid: usually a weekly injection for 2–5 weeks followed by monthly injections for 3–6 months [10]. This combination of surgical removal and corticosteroid injections has been shown to improve outcome. This dose of steroid is substantially more than the stat dose we plan to use in our study and requires multiple visits and repeated injections.

A thorough literature search has shown a lack of research on the surgical excision and injection of corticosteroid injection immediately after the excision of the existing caesarean section keloid scars. Therefore, in the proposed study, we aim to investigate the effect of corticosteroid (triamcinolone acetonide) injection immediately after surgical removal of old caesarean section keloid scars on the recurrence of the scars.

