### Outcome measures

#### Data collection sheet

A purposefully designed questionnaire consisting of two sections will be used to collect demographics (including age, country of birth, ethnic background, weight, height, BMI, number of previous vaginal births and/or caesarean sections, number of previous miscarriages, abortion and stillbirth, family history of keloid scars, history of any previous surgery and keloid scar on another site of body, gestational age at the time of baseline assessment) and any prior treatment of the keloid scar (section 1) and data on the keloid scar (section 2) including redness, hardness and elevation of the scar compared to the surrounding skin (0 = none, 1 = partially, 2 = entire scar). This section of the questionnaire also enquires about subjective symptoms of the scar including, but not limited to, itching, pain and swelling (0 = none, 1 = occasionally, 2 = all the time). The scar will be measured in millimetres using a hardened stainless steel 150mm Digital Vernier Caliper (Kincrome Pty Ltd, Scoresby, Australia) with a liquid-crystal display (LCD) screen to read an accurate measure to the nearest 0.02 mm. We will also take photographs of the scar to compare the visual changes. Section 2 of the questionnaire will be used at follow-up visits to collect data on the changes in the keloid scar. The same 150mm Digital Vernier Caliper will be used at follow-up visits, and the scars will be photographed again. To improve the objective validity of the trial and minimise recall bias of patients in the symptom scores, the participants will be shown photographs of the scar both before and one year after the intervention. They will be asked if they see any improvement before and after participating in the trial, both before and after seeing their scar photographs. In addition, the participants will assess and grade their satisfaction with the treatment on a 4-point scale (0 = no improvement/poor, 1 = fair, 2 = good, 3 = excellent). The participants will be queried on their overall satisfaction with the treatment (5 = very satisfied, 4 = slightly satisfied, 3 = neutral satisfaction, 2 = slightly unsatisfied, 1 = very unsatisfied). They will also be asked if they think they were in the intervention arm or the control arm of the trial before revealing this information to them at the final visit.

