### Randomisation

Through a parallel intervention assignment, the independent researcher will use a computer-Vgenerated random-numbers list to determine group allocation. The researcher will then place each allocation into sequentially numbered opaque envelopes. There will be permuted blocks of 10 with 1:1 allocation, containing 5 intervention and 5 control allocations in each block. This will help achieve balance across the two groups.

For those who are randomised to triamcinolone acetonide, the independent researcher will insert the medication inside the envelope and, after sealing it, will store the envelope in a locked cabinet inside the medication room in the birth unit. The surgeon who is rostered on the day of the caesarean section will be informed of the recruited participant and will be instructed on where to collect the concealed envelope. All participants will have their randomisation number indicated in the hospital electronic record at the time of study allocation. This is done to inform the researcher assessing the outcomes of the recruiting of the participant and the allocated number, but not the allocated intervention.

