### Data analysis

Intention-to-treat analysis will be performed using SPSS Advanced Statistics version 24.0 (SPSS, Chicago, IL, USA). Descriptive statistics will be used to summarise the demographic data; binary outcomes will be summarised with a relative risk (RR) and 95% confidence intervals (CIs) and compared between the two groups using a χ^2^ test (or Fisher’s exact test where applicable). Comparison of the number of patients with keloid formations within groups and between the two groups will be done using a χ^2^ test. A *t* test will be used to assess continuous non-skewed variables; these will be presented as means with standard deviations. For skewed ordinal data, the Mann–Whitney *U* test will be used; these data will be presented as medians with interquartile ranges. Difference in the effect over the sub-groups will be assessed using logistic regression. Outcomes of interest will be number of patients with keloid formation, changes in the appearance and specification of the keloid scar, depression, anxiety, stress and patient’s satisfaction. Changes in the appearance and specification of the keloid scar after the intervention will be summarised into two groups (binary outcome: 0 = changed, 1 = not changed) and will be analysed using logistic regression adjusting for the number of keloids formed and demographic variables. A *p* < 0.05 will be considered statistically significant.

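### Keloid formation, the first primary outcome, is analysed without the prognostic baseline factors the trial already records: a missed gain in precision, not a bias or a power shortfall

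*Protocol article*

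**What the plan says.** In the Data analysis section of the protocol article, the rule for keloid formation reads "Comparison of the number of patients with keloid formations within groups and between the two groups will be done using a" chi-square test. More generally, "binary outcomes will be summarised with a relative risk (RR) and 95% confidence intervals (CIs"), compared by chi-square or Fisher's exact test. No covariate is named for this outcome. The other primary outcome, change in the appearance and specification of the scar, "will be analysed using logistic regression adjusting for the number of keloids formed and demographic variables". Logistic regression is otherwise named only for sub-group differences in effect.

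The Data collection sheet section lists, among the baseline items, ethnic background, "family history of keloid scars, history of any previous surgery and keloid scar on another site of body", prior treatment of the scar, and scar measurements. The Background section says "Darkly pigmented skin is the primary risk factor for keloids". It also says of excision followed by steroid injection: "This has been suggested to be effective for patients with small or single site lesions". The Participants section admits women of all ethnicities.

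On allocation, the Randomisation section says "There will be permuted blocks of 10 with 1:1 allocation, containing 5 intervention and 5 control allocations in each block". No stratification factor is named.

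**The concern.** The protocol treats keloid risk as varying strongly between women, recruits across that range and records the factors, yet leaves them out of the main comparison. Permuted blocks balance the arm sizes, not keloid risk. The protocol accepts covariate adjustment for one primary outcome and gives no reason for omitting it for the other.

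The stake is the width of the interval for the main result. If recorded factors explain part of the variation in recurrence, conditioning on them removes that part from the error of the estimated arm difference at no cost in patients. Fixing the covariates in advance also avoids the argument that follows when a chance imbalance is noticed and adjustment is added afterwards.

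**Working it through.** **1. The plan's own sample size.** Inputs from the Sample size section: efficacy 45% v 70%, two-sided 5%, power 80%, 10% non-compliance, 75 per arm. With mean rate 0.575:

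n = [1.96·√(2·0.575·0.425) + 0.842·√(0.45·0.55 + 0.70·0.30)]² / 0.25² = [1.370 + 0.569]² / 0.0625 ≈ 60.2, so 61 per arm.

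With the continuity correction this becomes 68 per arm. Then 68 × 1.1 = 74.8, which is 75 per arm or 150 in total; 68/0.9 gives 76. The stated 150 is reproduced, as an unadjusted two-proportion comparison.

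**2. Power of the unadjusted test.** By the uncorrected normal approximation: 88% with 75 per arm and 85% with 68 per arm. As 61 per arm gives 80%, 120 women in total give about 80%.

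**3. Chance imbalance.** Assume a factor present in 40% of women. With 75 per arm, the SE of the difference in prevalence is √(0.4·0.6·2/75) = 0.08. A difference of at least 10 points corresponds to |z| ≥ 1.25, or about 21% of trials. Such imbalances are ordinary, and the chi-square's error rate already allows for them.

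**4. Gain from adjustment.** Simulation of 3000 trials per setting. Recurrence is 55% v 30%, the complements of 45% and 70%. Two binary baseline factors have assumed prevalence 40% and 30%. The odds ratios for recurrence are assumptions, since the document gives none. The crude risk difference with a pooled z-test is compared with the standardised risk difference from a logistic model with a Wald test. Ranges come from repeated runs.

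| Odds ratios | Women | Fall in variance | Power, crude to adjusted |
|---|---|---|---|
| 2, 2 | 150 | 2–3% | about unchanged (89% to 90%) |
| 3, 2 | 150 | 6–9% | 88% to 91% |
| 4, 3 | 150 | 12–14% | 89% to 92% |
| 4, 3 | 120 | 13% | 80% to 85% |

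A 14% fall in variance is worth 150 × (1/0.86 − 1) ≈ 24 women, and narrows the interval by 1 − √0.86 ≈ 7%. A 2% fall narrows it by about 1%. With no prognostic value, the adjusted variance was about 2% higher.

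**5. A second model.** One continuous risk score, 68 evaluable per arm, rates 45% v 70%, 3000 runs, logistic Wald test. Crude to adjusted power by log-odds per SD: 0, 84% to 84%; 0.5, 83% to 85%; 1.0, 85% to 91%; 1.5, 84% to 95%. To place step 4 on this scale, the SD of the combined log-odds is ln 2·√(0.24 + 0.21) ≈ 0.46 for odds ratios 2 and 2, and √(0.24·(ln 4)² + 0.21·(ln 3)²) ≈ 0.85 for 4 and 3. The 1.5 row is therefore well beyond the strongest binary setting and should not be used as the expected gain.

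**6. Type I error.** In step 5 the tests rejected under the null in 4.6–5.8% of runs. In the two-factor model with odds ratios 4 and 3 the rates were 6.5% crude and 6.1% adjusted. At 120 women the adjusted Wald test rejected in 5.6–6.2% against 4.8–5.7% for the crude test, so a little of the 5-point gain there may reflect a slightly liberal test.

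**The case against.** The strongest case against is that nothing here is wrong. An unadjusted chi-square with a relative risk is a valid analysis of a binary outcome in a 1:1 trial, keeps its error rate, and matches the calculation behind the 150. That stands, and it limits the point to efficiency.

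A reader might infer three stronger things that the document does not support:

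- **That the trial is underpowered.** Power is about 88% at 150 women and still about 80% at 120.
- **That chance imbalance in keloid risk biases the result.** Randomisation removes systematic imbalance, and the test and interval already allow for the random part.
- **That the gain must be large because of the stated strength of the main risk factor** ("Darkly pigmented skin is the primary risk factor for keloids, which has a 15–20 fold increased risk"). That figure concerns developing a keloid. Every participant already has one, so the trial selects on the event the factor predicts, and its value for predicting recurrence may be much weaker. The nearest support in the text is the remark on small or single-site lesions, which points to lesion size as well as to keloid elsewhere.

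It can also be said that covariate lists belong in a statistical analysis plan. That does not dispose of the point, because the protocol itself fixes the test for this outcome and names adjusters for the other primary outcome. Nor is the adjusted analysis of that outcome a pattern to copy as it stands: the number of keloids formed arises after randomisation.

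**Conclusion.** The point holds as a missed gain in precision. The unadjusted analysis is valid and the planned power is met. Under assumed odds ratios from 2 and 2 to 4 and 3, adjustment would reduce variance by about 2–14% and add about 0–3 points of power at 150 women. It would add about 5 points at 120 women under the strongest of these assumptions. If the recorded factors do not predict recurrence, there is no gain and a variance penalty of about 2%.

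These sizes rest on assumed prevalences and odds ratios, and on reading keloid formation as the complement of the efficacy rates in the Sample size section. The change is worth making because it is nearly free and the possible loss is small.

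**What to change.** For the final analysis of keloid formation, prespecify a logistic model with arm and a short set of baseline-only covariates already on the form: ethnic background in two or three groups, family history of keloid or keloid at another site, and baseline scar size. Report the risk ratio and risk difference standardised over all randomised women, each with a 95% CI, so that the effect measure stays comparable with the planned relative risk. Keep the chi-square as a supporting analysis.

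Do not include the number of keloids formed as a covariate. Do not apply the model at the interim look at 20 patients, where it would be unstable.

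The cost is a few sentences in the analysis section, a little more analysis work, and simple advance rules for grouping ethnic background and for missing covariates. No new data or patients are needed.

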**Methods/design:**

Pregnant women (*n* = 150), who attend antenatal clinics at Westmead Hospital in New South Wales, Australia, have a keloid scar from a previous caesarean section, meet the inclusion criteria and sign the consent form, will be randomised to either the control or the intervention group. The control group will receive surgical excision of the keloid scar at the beginning of the procedure during skin incision. The baby will be delivered according to normal procedures, and routine wound closure will be performed in accordance with National Institute for Health and Care Excellence guidelines. The intervention group will receive surgical excision of the keloid scar after the delivery of the baby, and closure of the uterus layers, rectus sheath and the fat layer will be completed as explained above. Then, triamcinolone acetone will be injected sub-dermally at the time of wound closure. Two ampules of triamcinolone acetonide will be administered at a single dose; each ampule contains 10 mg/1 ml active medication. The surgeon will inject one ampule along the entire length of the upper edge of the skin incision and one ampule along the entire length of the lower edge of the skin incision, using a 25 G needle. After the procedure is completed, the surgeon will fill in the post-operation survey.

The participants will be followed up post-operation, daily on the ward and then at 6 weeks, 6 months and 12 months post-partum. Main outcomes are (1) keloid formation after caesarean section and (2) changes in the appearance and specification of the keloid scar after the intervention.

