### Secondary objectives

Secondary objectives of the trial are to:Evaluate the effect of surgical excision and keloid scar treatment on symptoms of depression in women with keloid scarsDetermine whether surgical excision and sub-dermal injection of triamcinolone acetonide at the time of caesarean section changes the appearance (width, length, height) and specification (redness, hardness and elevation of the scar compared to the surrounding skin as well as discomfort including itching, pain and swelling) of the keloid scarAssess side effects of the surgical excision and sub-dermal injection of triamcinolone acetonide at the time of caesarean sectionInvestigate patients’ satisfaction with the treatment and their perception with the changes in their keloid scar after surgical excision and sub-dermal injection of triamcinolone acetonide at the time of caesarean section.

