### Follow-up

The follow-up period consists of 12 months face-to-face visits (Fig. 1). Post-operation, the patients will be visited daily on the ward for any signs of potential infectious local complications of the treatment and immediate side effects of the medication injection until the discharge home. The patients will then be visited in the women’s health clinic at the hospital for their 6th week post-partum check. The next follow-up times will be 6 months and 12 months post caesarean section. At each follow-up visit, the same assessment and scoring scales will be used to evaluate the changes to the keloid scar. Late side effects of the medication injection as well as symptoms of depression, anxiety and stress, and participants’ satisfaction will be assessed during follow-up visits at 6 weeks, 6 months and 12 months post-partum. The participants will also be asked if they would recommend such a procedure to another woman with a caesarean section keloid scar (yes/no) and if they would repeat the experience again in a future pregnancy (yes/no).

All measurements at baseline and follow-up visits will be performed by the same researcher, who will also make all efforts to ensure compliance with follow-up. As part of continuous clinical care, patients with any residue keloid scar with be given information on further treatment including referral to plastic surgeons if they are interested (Fig. 2).

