### Interim analysis

An interim analysis will be performed on the primary outcome of keloid formation in patients when enrolling 20 patients, including both the control and intervention groups, by a single statistician who is blinded to allocation and reports the results to the data and safety monitoring committee.

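### The composite primary outcome is two separate primary outcomes with no rule for combining them or for deciding success, and no primary visit

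*Protocol article*

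**What the plan says.** The sections Composite primary objective and Composite primary outcome each contain two items. The second item under Composite primary outcome reads "Changes in the appearance and specification of the keloid scar after the intervention". The abstract numbers them: "Main outcomes are (1) keloid formation after caesarean section and (2) changes in the appearance and specification of the keloid scar after the intervention".

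Data analysis gives each its own method. For the first: "Comparison of the number of patients with keloid formations within groups and between the two groups will be done using a" chi-square test. For the second: "Changes in the appearance and specification of the keloid scar after the intervention will be summarised into two groups", changed or not changed, analysed by logistic regression that adjusts for the number of keloids formed and for demographic variables. One sentence sets the threshold for everything: p < 0.05 "will be considered statistically significant".

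Other sections place the outcomes differently:

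- Secondary objectives asks whether the treatment "changes the appearance (width, length, height) and specification" of the scar, so the second primary outcome reappears as a secondary objective. Secondary outcomes does not list it.
- Interim analysis refers to "the primary outcome of keloid formation", in the singular.
- Sample size rests on one efficacy rate, 45% versus 70%, at two-sided 5% and 80% power. It does not say which outcome or visit that rate describes.

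On timing, Follow-up sets visits at 6 weeks, 6 months and 12 months and says: "At each follow-up visit, the same assessment and scoring scales will be used to evaluate the changes to the keloid scar". No section says which visit decides the trial.

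**The concern.** A composite outcome turns several components into one result per patient, which is tested once. Nothing of that kind is described here. The number of keloids formed even enters the model for appearance as a covariate, so the two cannot be parts of a single endpoint analysed together.

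The reader is left with two primary outcomes, each judged at the full 5%, and no statement of what makes the trial positive. Success on either, success on both, and success on keloid formation alone are all compatible with some part of the text, and they carry different false-positive risks. The missing primary visit adds a further choice. The result on which the trial stands could then be settled after the data are seen.

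**Working it through.** **1. The plan's own figure.** Inputs from Sample size: 45% versus 70%, two-sided alpha 0.05, power 80%, 10% non-compliance. The mean rate is 0.575.

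n per arm = [1.96·√(2·0.575·0.425) + 0.8416·√(0.45·0.55 + 0.70·0.30)]² / 0.25² = (1.370 + 0.569)² / 0.0625 ≈ 60.2, so 61.

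With continuity correction: (60.2/4)·[1 + √(1 + 4/(60.2·0.25))]² ≈ 67.95, so 68. Then 68 × 1.10 = 74.8, so 75 per arm and 150 in total. (Dividing by 0.9 gives 76 per arm, 152 in total.) The stated 150 is reproduced for one endpoint tested once at 5%. The fault lies in the definition of the endpoint, not in this arithmetic.

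**2. Two outcomes, one visit, success on either.** If independent: 1 − 0.95² = 9.75%. For correlated test statistics, the chance that at least one of two standard normal statistics exceeds 1.96 in absolute value is:

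| Assumed correlation | False-positive chance |
|---|---|
| 0 | 9.75% |
| 0.3 | 9.5% |
| 0.5 | 9.1% |
| 0.7 | 8.3% |
| 0.8 | 7.8% |
| 0.9 | 7.0% |

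The documents give no correlation, so these are assumptions. All values exceed 5%.

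**3. Two outcomes at three visits, success on any (hypothetical).** If independent: 1 − 0.95⁶ = 26.5%. With correlation 0.9 between outcomes and 0.9 between visits (product structure), simulation gives about 11.6%. With one common correlation of 0.9 among all six tests it gives about 10.9%.

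**4. Success required on both.** A false claim then needs both tests to be significant, so its probability is at most 5% at one visit. The protocol states no such rule.

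**5. Cost of keeping both as primary at 0.025 each,** assuming 45% versus 70% for each outcome: 74 per arm without continuity correction, and 74/0.9 gives 83, or 166 in total. With continuity correction it is 81 per arm, and 81/0.9 = 90, or 180 in total. The second is the like-for-like comparison with 150. At alpha 0.025, 75 evaluable per arm gives 81.2% power and 67 per arm gives 76.1% (both without continuity correction).

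**The case against.** Several points on the other side are sound, and they limit what can be claimed.

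- **No breach is written down.** Sample size attaches 5% to one comparison and claims no error rate across outcomes, and no either-outcome success rule appears. A reader might infer that the trial's 5% level is demonstrably broken. The text does not support that. It leaves out the decision rule, and the omission permits inflation.
- **Tests at every visit are not planned in the text.** Follow-up says only that the same scales are used each time, and Data analysis specifies no test by visit. A reader might take six tests, and 26.5%, as the plan. They are a hypothetical, and strong correlation between visits would lower the figure.
- **Sample size does not settle the primary outcome.** A reader might infer that it already treats keloid formation, yes or no, at 12 months as primary. It names an efficacy rate from a cited study, without outcome or visit. The first listed outcome, a reduction in amount, is not plainly binary either, although Data analysis does count patients.
- **The singular in Interim analysis is weak evidence.** It may only pick out one of the two listed outcomes.
- **A separate analysis plan could add multiplicity control.** It would have to override the single threshold printed here, and it could not make the sections agree on whether appearance is primary or secondary.

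What remains is the wrong label, the double status of appearance and specification, and two primary outcomes at p < 0.05 with no decision rule.

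**Conclusion.** The point holds as a defect of definition. The primary outcome is called composite but is two outcomes analysed separately, one of which is also a secondary objective. No section states what counts as success or at which visit.

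The firm part of the size is about 7% to 9.75% in place of 5%. It depends on success being claimable on either outcome and on an assumed correlation between 0.9 and 0. The range of about 11.6% to 26.5% applies only if both outcomes were tested at all three visits, which the protocol does not say. The sample size of 150 is sound for one endpoint tested once. This should be corrected before outcome data are seen by arm.

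**What to change.** Delete the word composite from both headings. Name one primary outcome at one visit, tested once at two-sided 5%. The proposed choice is the number of patients with keloid formation, which Data analysis and Interim analysis already use, at the final 12-month visit.

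State in Sample size that 45% versus 70% is the assumption for that endpoint, on the same scale. If efficacy means no keloid formation, the rates become 100 − 45 = 55% and 100 − 70 = 30% with keloid formation. That reading is an assumption for the investigators to confirm, because the section does not now define the rate.

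List appearance and specification as secondary, and the 6-week and 6-month visits as supportive. Align the abstract, Composite primary objective, Secondary objectives, Composite primary outcome, Secondary outcomes and Interim analysis.

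The cost is amendment wording and a registry update. The sample size stays at 150, and appearance loses its primary claim. If the investigators want to keep both outcomes as primary, they need a stated rule: split alpha (166 to 180 patients on the assumptions above), a fixed testing order, or a requirement that both succeed, with power recalculated for the last.
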